##### Process measures

In-depth interviews and FDGs will be conducted with CHWs in the intervention villages to explore facilitators and barriers to the implementation of the intervention and to understand the impact of the training on their daily work as a CHW. In addition, semi-structured interviews with end-users (e.g. patients) will be conducted to understand their experience of care and services provided by the CHW.

##### Intervention costing

We will analyse costs which will be confined to the costs of implementation and intervention, and the intervention impact will be defined as the reduction in the number of suicides in the experimental villages relative to the number in the control villages [37]. This will shed light on incremental costs per averted suicide. The costs will be estimated from a government provider perspective and economic costs (actual financial outlays and cost in time spent related to the intervention) will be considered [38]. We will also estimate the additional resource requirements for the government to scale the intervention.

An effective suicide prevention programme is defined as one that will lower the healthcare utilisation costs of people who attempt suicide and end up in the hospital emergency room (thus also quantifying the cost-offsets of the intervention). Cost-offsets could also occur when fewer people attempt suicide under the impact of the prevention programme, and thus continue to be productive members of society (less absenteeism from work). These cost-offsets outside the intervention will be calculated.

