#### Sample size and power calculation

The targeted effect of the SPIRIT intervention is to reduce suicide and attempted suicides by 20%. This target was validated through a series of interviews we carried out among Indian psychiatrists to build consensus on whether this would constitute a clinically meaningful outcome. This outcome will be measured using data on suicides and attempted suicides gathered through the surveillance system as described below. The sample size for each intervention was calculated separately in this cluster-randomised controlled trial.

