### Measures

The primary outcome of the integrated suicide prevention programme is a reduction in suicides and attempted suicides in the intervention villages compared to control villages. In addition, each intervention has its own primary and secondary outcomes (Table 1).

**Table 1 Tab1:** Primary and secondary outcomes of specific interventions of the cluster-randomised controlled trial

Interventions	Primary outcome	Secondary outcomes
Intervention 1: suicide prevention in schools through the Youth Aware of Mental Health (YAM) intervention	Reduction in suicidal ideation at 3-month and 12-month follow-up among adolescents in intervention schools	▪ Proportion of schools that agreed to implement the YAM intervention of the total number of schools approached for implementation ▪ Of those schools that agreed to implement the YAM intervention, the proportion of schools that implemented the programme ▪ Proportion of adolescents in intervention schools who received the YAM programme out of total number of adolescents in the selected grade
Intervention 2: community storage facilities (CSF) for pesticides	Reduction in the number of suicides and attempted suicides in intervention villages at 12-month follow-up	▪ Proportion of villages of those that were approached that agreed to have the CSF ▪ Proportion of villages that agreed to have the CSF or provided for or arranged space to build the storage facility ▪ Proportion of households reached with promotion activities linked to community storage of pesticides; proportion of households that requested a community storage box; proportion of households that received a community storage box ▪ Proportion of households in the villages that used the boxes regularly
Intervention 3: community health worker (CHW) training for identification, support and management of people at risk of suicide or self-harm	Number of persons with suicidal ideation detected by trained CHWs and number of persons referred by CHWs to mental health professionals for care for suicidal ideation	▪ Proportion of health workers trained in intervention villages ▪ Improvement in knowledge, skills, attitudes and practice of CHW who received training ▪ Number of CHWs applying knowledge and skills obtained through the training programme in their day-to-day practice at 6-month and 12-month follow-up

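### The costing takes suicides alone as its effect, although the trial is sized on suicides plus attempts, so cost per averted suicide would be too imprecise to use

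*Protocol article*

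**What the plan says.** The Intervention costing section of the protocol article states that "the intervention impact will be defined as the reduction in the number of suicides in the experimental villages", compared with control villages, and continues: "This will shed light on incremental costs per averted suicide". Attempted suicides appear in that section only on the cost side, as possible savings in emergency care and lost work. Of these it says: "These cost-offsets outside the intervention will be calculated".

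Elsewhere the effect is a composite. Under Measures, the programme's primary outcome is a "reduction in suicides and attempted suicides in the intervention villages compared to control villages". The section Sample size and power calculation targets a 20% reduction in that same composite. The sample size for intervention 2 assumes 10 composite events per 1,000 population and arrives at 73,092 persons per arm. The article states no expected number of suicide deaths.

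**The concern.** An incremental cost-effectiveness ratio is only as stable as its denominator. Here the denominator is a small subset of the events on which the trial was sized. Loose wording is an unlikely explanation, because the next paragraph of the same section refers separately to people who attempt suicide.

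If the expected difference in deaths is small against its own sampling error, the ratio can be very large, or change sign, through chance alone, even when the programme works. Policymakers would then receive a cost per averted suicide with no usable upper limit, while a far better-supported effect from the same surveillance system is left out of the economic result.

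**Working it through.** **Inputs (protocol article).** Persons per arm: 73,092. Households per village 522 and the figure 2,509, which I read as persons per village (2,509 / 522 = 4.8 per household), so 62 x 2,509 = 155,558 per arm. Suicide rates per 100,000: 11.8 (Gujarat, crime-records bureau), 15.7 (WHO, India), 62 (rural southern India). Composite planning rate: 10 per 1,000. Attempts per suicide: 10 to 40. Reduction: 20%. Follow-up: 12 months.

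**The plan's own figures.** 121,820 / 60,901 = 2.0003, an implied design effect of 2.0. 121,820 x 1.2 = 146,184, and half of that is 73,092. These steps reproduce. The starting figure of 60,901 does not: a standard two-sided comparison of 0.010 with 0.008 at 80% power needs 70,002 in total. That is a separate matter, and only the arm size and design effect are used here.

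**Formulas.** Control-arm deaths L0 = N x rate or, from the planning rate with k attempts per suicide, L0 = N x 0.010 / (k + 1). Intervention-arm deaths L1 = 0.8 x L0. Averted d = L0 - L1, SE = sqrt(L0 + L1), 95% interval d ± 1.96 SE. Power is approximately Φ(d/SE - 1.96). The chance of observing no reduction comes from the exact distribution of the difference of two Poisson counts. Clustering is ignored, which is optimistic.

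**Example.** 73,092 x 11.8 / 100,000 = 8.62 and 0.8 x 8.62 = 6.90, so d = 1.72. SE = sqrt(15.52) = 3.94, and 1.72 ± 7.72 gives -6.0 to 9.4.

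| Persons per arm | Source of deaths | L0 | Averted (95% interval) | Power | Chance of no observed reduction |
|---|---|---|---|---|---|
| 73,092 | 11.8 per 100,000 | 8.6 | 1.7 (-6.0 to 9.4) | 6% | 38% |
| 73,092 | 15.7 per 100,000 | 11.5 | 2.3 (-6.6 to 11.2) | 7% | 35% |
| 73,092 | 10 per 1,000, k = 40 | 17.8 | 3.6 (-7.5 to 14.7) | 9% | 29% |
| 73,092 | 62 per 100,000 | 45.3 | 9.1 (-8.6 to 26.8) | 17% | 17% |
| 73,092 | 10 per 1,000, k = 10 | 66.4 | 13.3 (-8.2 to 34.7) | 23% | 12% |
| 155,558 | 11.8 per 100,000 | 18.4 | 3.7 (-7.6 to 14.9) | 9% | 29% |
| 155,558 | 62 per 100,000 | 96.4 | 19.3 (-6.5 to 45.1) | 31% | 8% |
| 155,558 | 10 per 1,000, k = 10 | 141.4 | 28.3 (-3.0 to 59.6) | 43% | 4% |

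The last row is generous. It implies 1,000 / 11 = 91 suicides per 100,000, above every whole-population rate cited.

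**What 80% power would take.** (1.96 + 0.84)² x (1 + 1/0.8) / (ln 0.8)² gives about 355 control-arm deaths before clustering.

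**The composite.** At 73,092 per arm, 730.9 against 584.7 events, so 146.2 averted. With design effect 2.0, SE = sqrt(2 x 1,315.7) = 51.3, and the interval is 46 to 247 with power 81%.

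**Consequence for the ratio.** Where the interval for events averted includes zero, the corresponding interval for cost divided by events averted is unbounded. This is the expected situation in every suicide-only row, and not for the composite.

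**The case against.** Suicide rate is the development-goal indicator cited in the Background, so cost per averted suicide is a legitimate policy measure. A composite denominator would be 91% to 98% attempts (10/11 to 40/41) and would count an attempt the same as a death. Both points stand. They are reasons to show two ratios, not to drop one. Interval methods and acceptability curves can properly be left to an analysis plan that is not shown.

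Four stronger readings are tempting and are not supported:

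- A reader might infer that only 9 to 18 deaths per arm are expected. That uses the 11.8 rate alone, and the article itself says such records may substantially understate suicide. That rate also fits poorly with the planning rate: 1,000 / 11.8 is about 85 events per suicide, or 84 attempts, outside the cited 10 to 40. The wider range has to be shown.
- A reader might infer that the ratio cannot be estimated. A point estimate exists whenever fewer deaths occur in the intervention arm. What is lacking is precision.
- A reader might infer that the costing objective fails. The Background and Design sections state that objective as the cost of delivering the programme, which does not depend on the number of deaths.
- A reader might see a contradiction between "The costs will be estimated from a government provider perspective" and the counting of averted absenteeism. The text places these offsets outside the intervention and never says that they are netted into the ratio, so a contradiction is not shown.

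**Conclusion.** The concern holds as a mismatch between the costing effect and the effect the trial was sized to detect. Over every rate and attempt ratio examined, the 95% interval for suicides averted at a true 20% reduction includes zero before clustering. The chance that the trial's own interval would exclude zero is about 6% to 43%. At 9 to 18 control-arm deaths there is a 29% to 38% chance of seeing no reduction at all.

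This assumes one year of follow-up with the whole arm under surveillance, a 20% reduction that applies to deaths as it does to the composite, and 2,509 read as persons per village in the larger scenarios. Clustering would widen the intervals.

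The primary effectiveness test, the programme-cost estimate and the scale-up resource estimate are not affected. What is affected is the one cost-effectiveness ratio that the article promises.

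**What to change.** In the Intervention costing section, add incremental cost per suicide or attempted suicide averted, with the effect and its cluster-adjusted uncertainty taken from the primary model. Keep incremental cost per averted suicide beside it, with its interval and a plain statement that the trial was not sized for it and that it will be imprecise. State that the composite is mostly attempts and gives an attempt and a death equal weight, which is why both ratios are shown.

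The cost is a few sentences. The surveillance system already records both event types, so no new data are needed.

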### Adverse events

Even though the possibilities of adverse events directly related to the intervention are low, the SPIRIT study will maintain an incident register to record serious adverse events (SAEs) and adverse events (AEs). SAEs in this study are defined as attempted suicide, completed suicide, death due to other reasons or hospitalisation for an acute psychiatric crisis among students participating in the YAM intervention. AEs include emotional distress caused by a trial procedure (either the outcome assessments or the intervention delivery). Recognition of SAEs and AEs is a standard training module for all SPIRIT research team members. Ongoing identification of SAEs is monitored by the surveillance system data collection team. In the school-based intervention, information about any SAEs may be reported by parents, data collectors, teachers and/or school heads. For the community storage boxes, SAEs may be reported by the CHW and/or the attendant of the community boxes and/or any other community member. A protocol specifying questions for each SAE/AE has been established and each project team member trained in this protocol. Additionally, a protocol for reporting AEs to the Principal Investigator (PI), Data and Safety Monitoring Board (DSMB) and Institutional Review Board (IRB) is in place for the duration of the project.

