##### Intervention 1: school-based intervention (Youth Aware of Mental health (YAM))

The school-based intervention consists of a universal mental-health promotion programme in schools within intervention villages aimed at preventing depression, reducing suicidal ideation, and promoting mental health among students in grade 9 who are between 14 and 16 years of age. We chose this age group as suicide rates begin to increase from age 15 years onwards in South Asia [6]. In addition, psychopathological and behavioural changes often have their onset in adolescence, making mental health prevention and promotion particularly important in this target group [18, 19].

The school-based suicide prevention programme consists of a locally adapted version of the Youth Aware of Mental Health Programme (YAM), which has been effective in reducing suicide attempts and severe suicidal ideation among 14–15-year-old adolescents in a European multi-centre, multi-country, randomised controlled clinical trial [18]. YAM is an interactive programme for adolescents delivered within a teacher-free space, aiming to promote discussion and increase knowledge about mental health and the development of problem-solving skills and emotional intelligence. YAM is designed to help improve coping skills to deal with stressful life events that can trigger suicidal behaviours. YAM is a manualized 5-h programme broken down into 3-h of roleplay sessions and 2-h of interactive lectures and discussions about mental health at the beginning and end of the intervention. In addition, students receive a booklet on mental health issues and strategies to deal with difficult life events. Educational posters are available for each classroom; the themes of the posters are related to mental health and suicide, adapted by the SPIRIT research team to the local language and to the local setting in Gujarat [19].

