#### Intervention 1: YAM in schools: primary outcome

Suicidal ideation among young adolescents in both intervention and control condition schools will be assessed using the Suicidal Ideation Attributes Scale (SIDAS) [32]. SIDAS is a 5-item self-report scale addressing attributes of suicidal thoughts: frequency, controllability, closeness to attempt, level of distress associated with thoughts and impact on daily functioning. Scores ≥ 21 indicate a high risk of suicidal behaviour among youths. In this study, the SIDAS score will be assessed at baseline and at 3-month and 12-month follow-up. If a student has elevated scores on suicidal ideation (≥ 21 out of a maximum score of 50) at baseline assessment, he/she will be referred to the closest locally available health services such as a primary care centre, district mental health hospital or the Hospital for Mental Health in Ahmadabad (tertiary specialised mental health hospital).

Depression symptoms will be assessed using the Patient Health Questionnaire-9 (PHQ-9), a 9-item self-report scale [33, 34]. The PHQ-9 will be administered to students in the intervention and control schools at baseline and 3-month and 12-month follow-up. PHQ-9 scores range from 0 to 27 with higher scores indicating greater symptom severity. Scores of 5, 10, 15 and 20 represent cut-offs for mild, moderate, moderately severe and severe depression, respectively. Students who meet criteria for severe depression (scores > 20 on the PHQ-9 scale) at baseline assessment will be referred to the closest locally available health services such as a primary health centre, district mental health hospital or the Hospital for Mental Health in Ahmedabad (tertiary specialised mental health hospital).

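### The SAE definition is tied to YAM students: it clashes with the storage-box reporting sentence and, on either reading, leaves out control students' psychiatric admissions

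*Protocol article*

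**What the plan says.** The Adverse events section contains the article's only SAE definition. It begins "SAEs in this study are defined as attempted suicide, completed suicide, death due to other reasons" and ends with "hospitalisation for an acute psychiatric crisis among students participating in the YAM intervention". AEs are defined separately, as distress arising from either the assessments or the delivery of the intervention, with no limit to one arm.

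The same section then describes how SAEs come to light:

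- General route: "Ongoing identification of SAEs is monitored by the surveillance system data collection team".
- Schools: "In the school-based intervention, information about any SAEs may be reported by parents, data collectors, teachers and/or school heads".
- Storage facilities: "For the community storage boxes, SAEs may be reported by the CHW and/or the attendant of the community boxes and/or any other community member".

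No reporter is named for the CHW-training component as such, for control schools or for control villages. The section also refers to an established SAE/AE protocol and to a procedure for reporting to the PI, DSMB and IRB; neither is shown.

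On assessments, the section on the YAM primary outcome says: "The PHQ-9 will be administered to students in the intervention and control schools at baseline and 3-month and 12-month follow-up". SIDAS is likewise given in both arms at baseline, 3 months and 12 months.

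**The concern.** An SAE definition should say in whom an event counts. This one ends with a population phrase that can govern the whole list or only its last item, and neither choice gives a workable rule.

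Three things are at stake. First, field staff are trained to recognise SAEs from a definition that conflicts with the storage-box sentence a few lines later. Second, control students are exposed to a trial procedure (repeated questions about suicidal thoughts) which the section accepts may cause distress, yet at least one serious outcome of such distress is not an SAE for them. Third, an independent DSMB meets twice a year to oversee the trial. If student events are defined and sought more widely in one arm than in the other, a difference in counts could reflect the rule and not the programme.

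**Working it through.** The plan states no figure on this point, so the check sets the passages side by side.

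**Step 1. Two readings of the closing phrase**

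Reading A: the phrase governs all four events. Reading B: it governs hospitalisation only.

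| Event | Reading A: who is covered | Reading B: who is covered | Recorded by surveillance in both arms? |
|---|---|---|---|
| Attempted suicide | YAM students | no population limit stated | yes |
| Completed suicide | YAM students | no population limit stated | yes |
| Other death | YAM students | no population limit stated | not described |
| Psychiatric hospitalisation | YAM students | YAM students | not described |

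The last column comes from the section on the primary outcome of the integrated programme (monthly key informants, health facilities and police records on suicides and attempts) and from Data analysis and reporting, which compares the arms on surveillance data.

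**Step 2. Test each reading against the storage-box sentence**

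- Reading A: an adult poisoned with pesticide from a box is not a YAM student, so the event is not an SAE, yet reporters are named for storage-box SAEs. This is a contradiction.
- Reading B: an attempt, suicide or death linked to a box is an SAE, so the sentence makes sense. A psychiatric admission of an adult in the storage or CHW component still is not.

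**Step 3. Test each reading against the control students**

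- Reading A: none of their events is an SAE.
- Reading B: their attempts, suicides and other deaths are SAEs, but their psychiatric admissions are not.
- Common to both: control students' psychiatric admissions fall outside the definition, although they take the same scales at the same three time points.

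**Step 4. Test the sources**

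The school reporters are named for the school-based intervention, and box attendants exist only where there are boxes. For other deaths and psychiatric admissions among control students, the article therefore names neither a reporter nor a data source. Surveillance is also not described as linking a case to an enrolled student.

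**Step 5. Scale of the ambiguity**

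Inputs: 2278 students per arm (sample size for intervention 1); 73,092 persons per arm and 10 suicides or attempts per 1000 population (sample size for intervention 2). Assumptions: the rate covers one year and also holds for students. The 73,092 is a sample-size target that includes an attrition allowance, not a count of enrolled people.

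- Reading A, intervention arm: 2278 × 0.010 = 22.8, about 23 events.
- Reading B, intervention arm: 73,092 × 0.010 = 730.9, about 731 events, before any intervention effect.
- Ratio: 730.9 / 22.8 = about 32. Reading A covers 22.8 / 730.9 = about 3% of what Reading B covers.

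This shows only how far the reportable set moves with the reach of one phrase. It does not measure harm or bias.

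**The case against.** The strongest reply is that Reading B is the intended one. The surveillance team watches whole villages for SAEs, and any community member may report a storage-box SAE; both make sense only if some SAEs occur outside the YAM classes. A separate SAE/AE protocol exists, and an article may leave detail by component and by arm to it. The point touches neither the primary outcome nor its analysis.

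Much of this stands, and it rules out several stronger conclusions that a reader might draw:

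- *That the control arm can have no SAEs whatever happens.* This follows only under Reading A.
- *That the DSMB has no comparator.* Suicides and attempts are collected by the same surveillance in both arms.
- *That student attempts can no longer be compared.* Calling an attempt an SAE does not remove it from surveillance. The statement that YAM "which has been effective in reducing suicide attempts and severe suicidal ideation among 14–15-year-old adolescents" describes a European trial, and student attempts are not a separate outcome in Table 1.
- *That the storage component has no provision for SAEs.* It has named reporters; the fault is a conflict with the definition, not silence.
- *That the DSMB will see a one-arm SAE table.* The article does not say how SAEs are tabulated.

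What the reply does not remove is the gap that survives Reading B: psychiatric admissions are confined in terms to intervention students. That is a stated rule, not detail left elsewhere. The unseen protocol is described as specifying questions for each event, and nothing shown suggests that it changes the population.

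**Conclusion.** The point holds as an ambiguity and an asymmetry in the safety definition. Read literally, the definition contradicts the storage-box sentence. Read generously, it still excludes psychiatric admissions of control students and of adults. A comparison between arms is available for suicides and attempts; for other deaths and psychiatric admissions no control-arm source is described, so harm capture among students is unequal by arm.

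The students affected are the 2278 planned for control schools, half of the student sample. The number of missed events cannot be computed, because the article gives no rate for psychiatric admission or for other deaths. The conclusion rests on the article's wording alone; the SAE/AE protocol might already resolve it, in which case the article's definition should be brought into line. The consequence lies in safety monitoring, not in the primary analysis.

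**What to change.** Reword the Adverse events section in three respects.

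1. Apply one SAE definition to all enrolled students in intervention and control schools, with the same reporters (parents, data collectors, teachers, school heads) in both.
2. State which SAEs apply to the storage and CHW components, and in whom, so that the definition agrees with the storage-box sentence. Identical wording across arms cannot extend to these groups: boxes are offered only in intervention villages, and the CHW diary is described as a post-training record, so neither group has a described control counterpart.
3. Report student SAEs to the DSMB by arm, with the number of enrolled students as denominator, and use surveillance counts by arm for community suicides and attempts.

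The cost is a wording amendment, one table by arm in the twice-yearly DSMB report, and somewhat more event logging from control schools. Those schools are already visited for assessments, but other deaths and psychiatric admissions would have to come from the school reporters, since surveillance is not described as collecting them.
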